## Methods

### Study design

This 6-month pilot study will adopt a one-arm mixed method type 3 implementation-effectiveness hybrid design and be conducted in a single clinical site (see Figure 3). Type 3 hybrid designs emphasize testing the implementation strategy of an evidence-based intervention, but merely observing data collected on intervention effectiveness (Curran et al., 2012). While syntheses of effectiveness evidence for PROM use in routine care have typically found mixed results, with inconsistent impacts on patient outcomes (e.g., Boyce et al., 2013, Valderas et al., 2008), a more recent systematic review finds the evidence supports PROM use in standard care, particularly to improve patient-provider communication and decision-making in clinical practice (Isaque et al., 2019). The hybrid design also seems justified, given international momentum for PROM use (Rutherford et al., 2020), which may build with the COVID-19 pandemic. Indeed, there are calls for a scale up of electronic PROMs implementation in this crisis for the remote follow-up of chronic conditions, in part, to better screen patients and promptly manage their needs (Marandino et al., 2020).

Mixed methods were adopted in this study as multiple methods are recommended for studying intervention implementation and its problems in complex systems, like HIV clinics (Peters et al., 2013). Regarding the integration of the quantitative and qualitative data collected, this will occur toward study end within a convergent parallel design (Creswell and Plano Clark, 2011). Those directly involved in the analyses will decide upon the specifications of integration. Reporting of this study will seek to satisfy the standards of Good Reporting of a

Mixed Methods Study (O’Cathain et al., 2008) and the Standards for Reporting Implementation Studies (Pinnock et al. 2017).

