## Study metrics and instruments

Details on the constructs assessed; the instruments and metrics used; the chosen thresholds for success, if applicable; the participant group contributing data; and the timing of data collection are presented in Table 2. Many of the chosen metrics are based on those recommended by Stover et al. (2020). Importantly, the authors emphasize the need to standardize evaluation metrics in patient-reported measure implementation and to distinguish between those used to assess perceptions of the innovation and those used to assess the implementation strategy. Not meeting the set thresholds for success, in this study, will signify that modifications are necessary before proceeding to a definitive trial (Thabane et al., 2010).

Table 1. Schedule of study procedures for participants

| Procedure                                                  | Timeline               |                        |                        |                        |
|------------------------------------------------------------|------------------------|------------------------|------------------------|------------------------|
|                                                            | Prior to study start   | Study start (baseline) | Month 3                | Month 6                |
| Be screened and/or consent                                 | Patients
Physicians |                        |                        |                        |
| Attend educational meeting                                 | Physicians             |                        |                        |                        |
| Receive training on the I-Score measure and Opal           | Patients
Physicians | Patients
Physicians | Patients
Physicians | Patients
Physicians |
| Complete the I-Score measure via Opal                      |                        | Patients               | Patients               | Patients               |
| Examine the I-Score measure results via the ORMS dashboard |                        | Physicians             | Physicians             | Physicians             |
| Attend HIV patient-physician visit (online or in person)   |                        | Patients
Physicians | Patients
Physicians | Patients
Physicians |
| Complete the post-visit checklist                          |                        | Physicians             | Physicians             | Physicians             |

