Regarding the patient outcomes of Objective 3, barriers to adherence and adherence will be summarized with the minimum, the maximum, the mean, and the standard deviation. Viral load will be reported by absolute and relative frequencies, as it is considered a dichotomous variable. For the service outcome obtained from the physician checklist, we will report the proportion of clinic visits when physicians took action based on the I-Score results, among the visits where an adherence barrier of concern was identified by physicians. Proportions will be reported for T1, T2 and T3 and globally, across time periods. To evaluate evidence of a statistically significant difference in our chosen effectiveness outcomes, we will run a Student's paired t-test for barriers to adherence and adherence and a McNemar test for viral load, between T1 and T3. To complete the analysis of the service outcome, we will use a logistic regression model, considering only the visits where an adherence barrier of concern was identified by physicians. The dependent variable is the binary variable of whether or not an action was taken by physicians and the independent variable is the time, considered as a factor with three independent levels (T1, T2 and T3). We will test the null hypothesis that time has no effect on the probability of taking action, with a t-test on the regression coefficient. We will conclude the analysis by testing the null hypothesis of equality of proportions between all pairwise combinations of time points, with a Student's t-test between two proportions, performing a Bonferroni correction for multiple tests. For all analyses, a significance level of 5% will be adopted.

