|                         | Ensure open channels of communication with time and space for clinicians to criticize and feedback on the PROM process | Process: Reflecting & evaluating | -                                   | Plan: Organize clinician implementation team meetings                                                                                                                                                                                                                    |
|                         | Implementation leads must consider feedback and use it to develop the process                                          | Process: Reflecting & evaluating | -                                   | Quality management: Conduct cyclical small tests of change

Building on feedback received from patients and physicians and the Application Manager's field notes, we will use a rapid-cycle evaluation approach, using the CFIR, to improve implementation. |

*Note.* PROM = patient-reported outcome measure; CFIR = Consolidated Framework for Implementation Research; \* Reproduced or adapted from Foster et al. (2018); \*\* Based on Damschroder et al. (2009); \*\*\* Based on the taxonomies of Powell et al. (2012, 2015).

Table 3. Implementation science metrics and effectiveness outcomes collected for the pilot study.

| Objective                                                                                   | Construct                 | Data collected                                                                                              | Threshold for success | Participant group |            | Timing     |
|---------------------------------------------------------------------------------------------|---------------------------|-------------------------------------------------------------------------------------------------------------|-----------------------|-------------------|------------|------------|
|                                                                                             |                           |                                                                                                             |                       | Patients          | Physicians |            |

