| Objective 3
– Determine preliminary intervention effectiveness & outcome measure utility | Patient management        | Checklist of physician actions following review of the I-Score results                                      | $p \leq 0.05$         | -                 | ✓          | T1, T2, T3 |
|                                                                                             | Barriers to ART adherence | The I-Score PROM                                                                                            | $p \leq 0.05$         | ✓                 | -          | T1, T2, T3 |
|                                                                                             | Adherence to ART          | Self-Rating Scale Item (Feldman et al., 2013)                                                               | $p \leq 0.05$         | ✓                 | -          | T1, T2, T3 |
|                                                                                             | Viral load                | The HIV RNA viral load, as indicated in the patient's medical file (> 50 copies = detectable)               | $p \leq 0.05$         | ✓                 | -          | T1, T3     |

PROM: patient-reported outcome measure; ART: antiretroviral therapy. \* Qualitative data include the Application Manager's notes (T1-T3), the qualitative interviews with patients and the focus groups with physicians (T2, T3).

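### The success threshold of p ≤ 0.05 for patient management tests change between visits that all carry the I-Score, so steady full action fails and a decline can pass; the other three Objective 3 rows name no direction of benefit

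*Protocol*

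**What the plan says.** Table 3 of the Protocol has a column headed "Threshold for success". In each of the four Objective 3 rows (patient management, barriers to adherence, adherence, viral load) that column holds only p ≤ 0.05. The rows of Objectives 1 and 2 that have a threshold use a level instead, such as a mean of at least 24 or a proportion of at least 80%.

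The patient-management row is the "Checklist of physician actions following review of the I-Score results". Under Quantitative analysis, the Objective 3 paragraph fits a logistic regression to the visits where the physician identified a barrier of concern, with time "considered as a factor with three independent levels (T1, T2 and T3"). It continues: "We will test the null hypothesis that time has no effect on the probability of taking action, with a t-test on the regression coefficient". Bonferroni-corrected comparisons of all pairs of time points follow. The same paragraph also plans to report the proportion of concern visits with an action, by time point and overall, with no threshold attached. Barriers and adherence get a paired t-test, and viral load a McNemar test, between T1 and T3. On the error rate it says: "For all analyses, a significance level of 5% will be adopted". Sidedness is not stated.

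Under The I-Score intervention, patients complete the measure before each of the three visits, T1 included.

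Study metrics and instruments says: "Not meeting the set thresholds for success, in this study, will signify that modifications are necessary before proceeding to a definitive trial". Study design describes a type 3 hybrid as "merely observing data collected on intervention effectiveness".

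**The concern.** Objective 3 asks whether the intervention shows promise. For patient management, promise means that physicians act when the I-Score shows a barrier of concern. That is a level, and the written criterion tests a change. Because the I-Score is in use at T1, T2 and T3, a change between those visits says whether action drifted during exposure. It does not say whether the I-Score prompts action. The best possible result therefore cannot count as success, and a loss of physician engagement can.

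For the three patient outcomes the structure is sounder, since T1 can serve as a near-baseline. There the gap is only that nothing in Table 3 or the analysis text says which direction is success.

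At stake is the Objective 3 conclusion carried into the planning of the definitive trial.

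**Working it through.** The Protocol gives no sample-size or power figure for Objective 3, so there is no stated figure to reproduce. The p ≤ 0.05 of Table 3 agrees with the 5% level in Quantitative analysis. The check applies the planned tests to example data.

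**Inputs.** 30 patients (Setting and participants), hence at most 30 concern visits per time point. Time is a three-level factor, and the three pairwise tests are made at 0.05/3 = 0.0167 (Quantitative analysis). The number of concern visits is not given, so 10, 20 and 30 per time point are assumed. Visits are treated as independent, as in the planned logistic model.

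**1. Steady action.** With the same proportion at T1, T2 and T3, the model with time fits no better than the model without it. The likelihood-ratio statistic is 2 × (logL with time − logL without time) = 0 on 2 df, so p = 1.00.
- Action at 30/30, 30/30, 30/30: both log-likelihoods are 0, p = 1.00. No visit lacks an action, so the coefficients are not identified and the pairwise tests have zero variance. The same holds for 20/20 and 10/10.
- Action at 2/20, 2/20, 2/20: both log-likelihoods are −19.505, p = 1.00.

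The criterion gives the same answer for 100% and 10% action. This does not depend on the assumed counts.

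**2. Declining action: 27/30, 22/30, 15/30 (90%, 73%, 50%).**
- Likelihood ratio: 2 × (−47.944 + 54.104) = 12.32 on 2 df, p = 0.0021.
- T3 v T1 coefficient: ln(15/15) − ln(27/3) = −2.197; standard error √(1/27 + 1/3 + 1/15 + 1/15) = 0.710; ratio −3.10, p = 0.0020.
- Pairwise T1 v T3: pooled proportion 42/60 = 0.70; z = (0.90 − 0.50)/√(0.70 × 0.30 × 2/30) = 3.38, p = 0.0007, below 0.0167.

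The threshold is met. The mirror-image rise, 15/30, 22/30, 27/30, gives the same three p-values.

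**3. Fewer concern visits.**

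| Visits per time point | Actions at T1, T2, T3 | Likelihood-ratio p | T3 v T1 coefficient p |
|---|---|---|---|
| 20 | 18, 14, 10 | 0.017 | 0.011 |
| 10 | 9, 6, 4 | 0.0496 | 0.035 |

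Both declines meet p ≤ 0.05. In the last row the pairwise T1 v T3 test (p = 0.019) does not pass the Bonferroni limit of 0.0167.

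**4. Patient outcomes, if the tests are two-sided.**
- Paired t, n = 30, standardized change of +0.4 or −0.4: |t| = 0.4 × √30 = 2.19 on 29 df, p = 0.037 either way.
- McNemar (exact version), 8 patients worsening and 1 improving: p = 2 × (1 + 9)/2⁹ = 0.039, the same as 1 worsening and 8 improving.

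**The case against.** Much of the case on the other side is sound and limits the point.

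- *Is the modification rule triggered?* A reader might infer that missing p ≤ 0.05 on Objective 3 obliges the team to modify the intervention. The documents do not support that. Quantitative analysis ties the targets for proceeding to most metrics of Objectives 1 and 2, and effectiveness is only observed. The rule speaks of modifications in general, which could be to methods or outcomes. But its sentence exempts no objective, and Table 3 puts all objectives in one threshold column. Its reach is ambiguous and needs stating.
- *Are the tests two-sided?* The Protocol does not say; the wording in terms of difference and equality only suggests it. An SAP could make them one-sided, and a sensible reader would not call more detectable viral loads promising. With a true benefit of d = 0.3, a significant result in the wrong direction has a probability below 0.05% at n = 24 or 30, so passing through worsening would in practice require real worsening. This answers most of the concern for the three patient outcomes. It does not help patient management, where a one-sided test for a rise still fails steady 100% action.
- *Will a useful intervention usually fail the patient-outcome rows?* That depends on the assumed effect. For the paired t-test, power at n = 24 and 30 is 29% and 36% at d = 0.3, but 65% and 75% at d = 0.5. Nor is there a fixed minimum number of discordant pairs for viral load: an exact McNemar test needs six, all one way (p = 0.031), while the uncorrected chi-square version passes with four (p = 0.046). The Protocol does not say which version applies. No such claim is made here.
- *No control group.* That belongs to the declared one-arm design and is not an error in Table 3.
- *The right quantity is already planned.* True: the action proportions will be reported by time point and overall. Only the success criterion is attached to the wrong quantity.

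**Conclusion.** The point holds for patient management without reservation. The threshold is fixed in the Protocol, so it is not a detail left to an SAP, and it cannot be met by steady action at any level or sample size, while a marked decline meets it. The p-values for a decline (0.002 with 30 concern visits per time point, 0.017 with 20, 0.0496 with 10, by likelihood ratio) rest on assumed counts and independent visits. The failure at steady 100% rests on neither.

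For barriers, adherence and viral load the point is narrower: the threshold lacks a direction, so read literally a significant worsening meets it. A reader might conclude that p ≤ 0.05 must be removed from those rows as well. The defect does not require that, because T1 to T3 is a usable contrast and a stated direction repairs the criterion.

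This should be fixed, but it is not critical. Objective 3 is secondary, and the primary acceptability outcome and the thresholds of Objectives 1 and 2 are unaffected.

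**What to change.** 1. **Table 3, patient management.** Replace p ≤ 0.05 with the proportion of concern visits with an action, overall and per time point, with its 95% confidence interval. Set it against a numeric target chosen by the team if one is wanted, as in the rows of Objectives 1 and 2. In Quantitative analysis, keep the time-effect test and label it descriptive.
2. **Table 3, other three rows.** State the favourable direction (fewer barriers, higher adherence, fewer detectable viral loads) and report the T1-to-T3 change with its 95% confidence interval.
3. **Study metrics and instruments.** State that the modification rule applies to the thresholds of Objectives 1 and 2, in line with Quantitative analysis and Study design.

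The cost is four table cells, one sentence in Study metrics and instruments, and small edits to the Objective 3 paragraph of Quantitative analysis. No additional data or patients are needed. The downside is that the patient-management row no longer supports a success claim based on significance.

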## Appendix

## Refusal form

- 1- What is your year of birth? \_\_\_\_\_
- 2- What is your sex?
- ☐ Female
  - ☐ Male
  - ☐ Trans
- 3- What is your preferred language?
- ☐ French
  - ☐ English
  - ☐ Other (please specify): \_\_\_\_\_
- 4- What is the main reason why you do not wish to participate in this study?
- ☐ I am not comfortable using smartphone apps
  - ☐ I am concerned about confidentiality
  - ☐ I am not interested in this study
  - ☐ I do not have the time
  - ☐ Other (please specify): \_\_\_\_\_

Time 1 questionnaire for people living with HIV

***Your sociodemographic characteristics***

*The following questions concern your sociodemographic characteristics.*

- 5- What is your year of birth? \_\_\_\_\_
- 6- What is your sex?
- ☐ Female
  - ☐ Male
  - ☐ Trans
- 7- What is your preferred language?
- ☐ French
  - ☐ English
  - ☐ Other (please specify): \_\_\_\_\_
- 8- What is the highest level of education that you have completed?
- ☐ Primary
  - ☐ Secondary (High school)/Professional degree
  - ☐ College/ Cegep/ Technical degree
  - ☐ University
  - ☐ Other (please specify): \_\_\_\_\_
- 9- What is your annual income (\$CAD)?
- ☐ Less than \$10,000
  - ☐ \$10,000-\$19,999
  - ☐ \$20,000-\$39,999
  - ☐ \$40,000-\$59,999
  - ☐ \$60,000-\$79,999
  - ☐ \$80,000-\$99,999
  - ☐ Greater than \$100,000
- 10- Did you immigrate to this country?
- ☐ Yes
  - ☐ No
- 11- What ethnic group(s) or family background(s) do you identify with? Select all that apply.
- ☐ Aboriginal or Indigenous
  - ☐ English Canadian
  - ☐ French Canadian
  - ☐ French
  - ☐ British
  - ☐ Other Easter/Western European
  - ☐ East Asian
  - ☐ South Asian
  - ☐ West Asian
  - ☐ Arab or North African
  - ☐ Latin American
  - ☐ African
  - ☐ Black
  - ☐ Caribbean
  - ☐ Pacific

- ☐ Mixed race/ethnicity
- ☐ Other (please specify): \_\_\_\_\_

12- Which of the following best describes your sexual orientation?

- ☐ Heterosexual
- ☐ Homosexual
- ☐ Bisexual

### ***Your HIV diagnosis and medication***

*The next two questions concern your HIV diagnosis and HIV medication.*

13- What year were you diagnosed with HIV? \_\_\_\_\_

14- How would you rate your overall satisfaction with your current HIV medication?

- ☐ 1—very dissatisfied
- ☐ 2
- ☐ 3
- ☐ 4
- ☐ 5—very satisfied

### ***Your use of mobile devices***

*These next questions concern your use of mobile devices.*

15- With what frequency do you use mobile devices (smartphone, tablet computer, cell phone, smartwatch, pocket PC, etc.)?

- ☐ Several times a day
- ☐ Once a day
- ☐ Several times per week
- ☐ Several times per month

16- On your tablet or smartphone, do you have any ‘apps’ related to health and wellness?

- ☐ Yes
- ☐ No

17- To what extent do you use applications related to health on a mobile device?

- ☐ Several times a day
- ☐ Once a day
- ☐ Several times per week
- ☐ Several times per month
- ☐ Once a month or less
- ☐ Never

*Please indicate your level of agreement with the following statements.*

18- I am confident that I can effectively report medical information using mobile technology.

- ☐ Strongly agree
- ☐ Agree
- ☐ Neutral
- ☐ Disagree
- ☐ Strongly disagree

19- If any health care provider asks me to report personal health data using a mobile device app, I will do so.

- ☐ Strongly agree
- ☐ Agree
- ☐ Neutral
- ☐ Disagree
- ☐ Strongly disagree

***Your thoughts on using the I-Score***

*In this section, the questions are about your thoughts on using the I-Score measure, as completed through the Opal app.*

2. How easy was the I-Score for you to use?
  - ☐ 1—very difficult
  - ☐ 2
  - ☐ 3
  - ☐ 4
  - ☐ 5—very easy
  
3. How understandable were the questions?
  - ☐ 1—difficult to understand
  - ☐ 2
  - ☐ 3
  - ☐ 4
  - ☐ 5—easy to understand
  
4. How much did you enjoy using the I-Score?
  - ☐ 1—not at all
  - ☐ 2
  - ☐ 3
  - ☐ 4
  - ☐ 5—very much
  
5. How helpful was the I-Score in describing difficulties experienced taking HIV medication?
  - ☐ 1—very unhelpful
  - ☐ 2
  - ☐ 3
  - ☐ 4
  - ☐ 5—very helpful
  - ☐ Not applicable
  
6. Was the amount of time it took to use the I-Score acceptable?
  - ☐ 1—very unacceptable
  - ☐ 2
  - ☐ 3
  - ☐ 4
  - ☐ 5—very acceptable
  
7. How would you rate your overall satisfaction with the I-Score?
  - ☐ 1—very dissatisfied
  - ☐ 2
  - ☐ 3
  - ☐ 4
  - ☐ 5—very satisfied

8. How likely are you to recommend the I-Score?

- ☐ Extremely unlikely
- ☐ Unlikely
- ☐ Neither likely nor unlikely
- ☐ Likely
- ☐ Extremely likely

| 9. Using the I-Score seems... | Completely disagree | Disagree | Neither agree nor disagree | Agree | Completely agree |
|-------------------------------|---------------------|----------|----------------------------|-------|------------------|
| a. fitting                    | ①                   | ②        | ③                          | ④     | ⑤                |
| b. suitable                   | ①                   | ②        | ③                          | ④     | ⑤                |
| c. applicable                 | ①                   | ②        | ③                          | ④     | ⑤                |
| d. like a good match          | ①                   | ②        | ③                          | ④     | ⑤                |
| e. implementable              | ①                   | ②        | ③                          | ④     | ⑤                |
| f. possible                   | ①                   | ②        | ③                          | ④     | ⑤                |
| g. doable                     | ①                   | ②        | ③                          | ④     | ⑤                |
| h. easy                       | ①                   | ②        | ③                          | ④     | ⑤                |

